## STATISTICAL ANALYSES AND REPORTING PLAN

3

### Clinical efficacy

3.1

We will report clinical efficacy findings with and without data imputations under the intention‐to‐treat analysis and missing data assumptions (e.g., completer's analysis). The intention‐to‐treat approach will involve all outcomes being evaluated and imputed for all participants who were randomized and provide baseline data, consistent with previous research.^32^, ^46^

Clinical efficacy will be assessed utilizing longitudinal GEE models to assess changes in the primary and secondary clinical outcomes over time and between the three groups.

Post‐treatment is the primary endpoint for changes in the primary and secondary clinical outcomes. To determine whether post‐treatment improvements are maintained over time, within‐group time effects will be examined at 3‐ and 12‐month follow‐ups. For all analyses, the level of statistical significance will be set at alpha 0.05. All GEE models will include log‐link function and gamma scale parameters to account for the positive skew in the clinical outcome data.

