### Procedures

2.6

The Wellbeing Neuro Course will be employed as the intervention in this study and is a digital psychological treatment for adults with neurological disorders.^31^ This intervention has been carefully developed to be suitable for adults with a broad range of neurological disorders, including PWE. It uses the principles of both cognitive behavior therapy and compensatory cognitive rehabilitation to target several domains of mental health and functional disability and covers a range of skills for managing depression, anxiety, cognitive difficulties, and activity/fatigue levels. A comprehensive overview of the intervention has been previously reported.^31^ A previous RCT of the intervention in a guided format found significant benefits on measures of depression, anxiety, disability, and cognitive function in the treatment group relative to the TAU‐WLC.^32^ Participants included a mixed sample of PWE, MS, Parkinson's disease, or an acquired brain injury. Acceptability of the treatment was also high, with over 90% of participants reporting that the course was worth their time and that they would recommend it to others.

The course includes six online lessons which are provided over a 10‐week period. Participants will work through the course according to a predetermined timetable and cannot access new materials without first having read previous materials. The course also includes worksheets for each lesson, additional written resources that can be downloaded, and case stories based on previous participants which can be followed throughout the course.

Participants allocated to the guided group will have access to support from an eCentreClinic clinician as they work through the course. All clinicians will be mental health professionals and will be employed by Macquarie University or one of its entities (e.g., MQ Health). All mental health professionals will be provided with training and supervision from a senior clinical psychologist to ensure competence and safety in their practice.

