Participants in the guided group will be informed that their clinician will be available for approximately 15 min each week and will contact them throughout the course via telephone or secure messaging systems, with more time available if clinically indicated. Clinicians will be available to (1) answer questions; (2) summarize content; (3) encourage skills practice and reinforce progress; (4) enquire about participants' use of the skills; and (5) normalize challenges.

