### Power and sample size

2.9

Sample size was determined in line with expert guidelines^43^ and calculations included data from a previous RCT, which observed a standard rate of symptom change on our primary outcomes of depression and anxiety of 24% each.^32^ We utilized specialized longitudinal software^44^ to account for our proposed generalized estimation equations models (GEE). Power analyses were conducted with Type I error set at α = 0.05 and Type II error at β = 80% and utilized a DELTA2 methodology.^43^

Our superiority analyses will compare the two active treatment groups with the TAU‐WLC. We calculated that this requires a sample size of 125:80 (e.g., unguided: control) to detect a difference in the rate of symptom change as small as 11% on the mental health primary outcomes from baseline to post‐treatment.^44^ Our noninferiority analyses will compare the unguided and guided treatment groups. In line with power estimation for non‐inferiority thresholds^44^ in mental health trials,^45^, ^46^ we considered a difference of 50% of the standard rate of symptom reduction in depression and anxiety symptoms (i.e., 12% reduction in symptoms at post‐treatment) as the prespecified margin of noninferiority.^47^ Based on these margins, we require a sample size of 125:125 (unguided: guided).

Utilizing a conservative attrition estimate of 20%, a final larger sample of 150:150:75 (“Guided: Unguided” control) was decided.

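### No stated allowance for clinician clustering in the guided arm: if outcomes correlate within clinician, guided-arm intervals will be too narrow and the 80% power overstated

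*Protocol article*

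**What the plan says.** Participants are randomised individually, 2:2:1, to guided, unguided and waitlist arms (section 2.6.1). On delivery, section 2.6 (Procedures) says: "Participants allocated to the guided group will have access to support from an eCentreClinic clinician as they work through the course". Guided participants are told that "their clinician will be available for approximately 15 min each week and will contact them throughout the course". Clinicians are referred to in the plural, and neither their number nor their caseload is given. Section 2.2 describes the unguided arm as having no clinician support. The waitlist arm is not offered the course until about 6 months from baseline, after the post-treatment endpoint. Every applicant who passes online screening has a clinician interview (section 2.4), but that precedes treatment and is common to all arms.

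Section 3.1 names the primary model as "longitudinal GEE models to assess changes in the primary and secondary clinical outcomes over time and between the three groups", with log link and gamma scale, and makes post-treatment the primary endpoint. It states no cluster unit and no clinician term. The sensitivity analyses in section 3.3 do not mention clinicians.

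Section 2.9 lists what went into the sample size: the "standard rate of symptom change on our primary outcomes of depression and anxiety of 24% each" from a previous trial, longitudinal software used "to account for our proposed generalized estimation equations models (GEE"), the error rates, the margins and 20% attrition. It arrives at 125:125 for non-inferiority and 125:80 for superiority over control. No ICC, caseload or design effect appears.

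**The concern.** This is a partially nested design. In the guided arm, participants who share a clinician may have correlated outcomes; in the other arms each participant stands alone. The nesting also coincides with the ingredient under test, because guidance is what separates the two active arms. A longitudinal GEE that clusters on participant handles repeated measures. Its robust variance does not cover correlation between different participants of the same clinician.

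For non-inferiority the error runs in the unsafe direction. An interval that is too narrow makes it easier to conclude that unguided care is not inferior, which is the second hypothesis in the Introduction and the result most likely to influence which model services adopt. The guided-versus-control comparison is affected in the same way. The unguided-versus-control comparison is not.

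**Working it through.** **Inputs from section 2.9**
- Error rates: "Type I error set at α = 0.05 and Type II error at β = 80"%. I read the second figure as 80% power. Sidedness is not stated, so both one-sided 0.05 and one-sided 0.025 are shown.
- Margin: half of 24%, that is 12 points ("12% reduction in symptoms at post‐treatment").
- Sizes: 125:125 and 125:80.

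**Assumptions, not in the article**
- Clinician ICC 0.01 to 0.05; number of clinicians k = 5, 10 or 15; equal caseloads.

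**The plan's own figure.** The article gives no standard deviation, within-person correlation or sidedness, so 125:125 cannot be reproduced. It can only be inverted: SD = 12 / [(z_alpha + 0.842) × √(2/125)]. This gives 38.2 points at one-sided 0.05 and 33.9 points at one-sided 0.025. I therefore take 125:125 as giving exactly 80% power under independence and ask what clustering does to it.

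**Formulas**
- Design effect, guided arm only: DE = 1 + (125/k − 1) × ICC
- Ratio of true to independence standard error: r = √[(DE/n1 + 1/n2) / (1/n1 + 1/n2)], with n1 the guided arm
- Error rate of a test that ignores clinician: P(Z > z_alpha / r), doubled if two-sided
- Power of a test with the right variance: Φ[(z_alpha + 0.842)/r − z_alpha]

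**Worked example** (k = 5, ICC 0.05, one-sided 0.05): DE = 1 + 24 × 0.05 = 2.20; r = √[(2.20 + 1)/2] = 1.265; error = P(Z > 1.645/1.265) = 9.7%; power = Φ(2.487/1.265 − 1.645) = 62.6%.

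**Non-inferiority, 125:125: error / power**

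| Clinicians | ICC | DE | r | One-sided 0.05 | One-sided 0.025 |
|---|---|---|---|---|---|
| any | 0 | 1.00 | 1.000 | 5.0% / 80% | 2.5% / 80% |
| 5 | 0.01 | 1.24 | 1.058 | 6.0% / 75.9% | 3.2% / 75.4% |
| 5 | 0.02 | 1.48 | 1.114 | 7.0% / 72.2% | 3.9% / 71.1% |
| 5 | 0.05 | 2.20 | 1.265 | 9.7% / 62.6% | 6.1% / 60.1% |
| 10 | 0.01 | 1.115 | 1.028 | 5.5% / 78.0% | 2.8% / 77.8% |
| 10 | 0.05 | 1.575 | 1.135 | 7.4% / 70.8% | 4.2% / 69.5% |
| 15 | 0.01 | 1.073 | 1.018 | 5.3% / 78.7% | 2.7% / 78.6% |
| 15 | 0.05 | 1.367 | 1.088 | 6.5% / 73.9% | 3.6% / 73.1% |

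A simulation of the ICC 0.05 case (20,000 runs, one-sided 0.05) gave error rates of 9.8% for 5 clinicians and 7.4% for 10, in line with the formula.

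**Guided versus control**, 125:80, two-sided 0.05, 80% power under independence: k = 5 and ICC 0.05 gives r = 1.212, error 10.6%, power 63.8%; k = 15 and ICC 0.01 gives r = 1.014, error 5.3%, power 78.9%.

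**Few clinicians.** The power figures above treat the variance as known. With v1 = DE/125 and v2 = 1/125, the Satterthwaite degrees of freedom are (v1 + v2)² / [v1²/(k − 1) + v2²/124]. For k = 5 and ICC 0.05 this is 0.0256² / (0.0176²/4 + 0.008²/124) ≈ 8.4. A t-test on that basis has about 56% power at one-sided 0.05 and 50% at one-sided 0.025.

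**The case against.** Four objections deserve an answer.

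1. **The analysis half rests on silence.** Section 3.1 does not name the cluster unit, and a condensed article may leave it to an analysis plan that is not shown. A reader might infer that the primary GEE definitely treats guided participants as independent. The text does not establish that: the quoted sentence would also fit a model clustered on clinician. The sample-size half is firmer, because section 2.9 sets out its ingredients and clinician clustering is not among them. A later analysis plan cannot change how 125:125 was derived.

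2. **The ICC may be very small.** Lessons are fixed online content on a set timetable, contact is about 15 minutes a week on a short list of supportive tasks, and all clinicians are trained and supervised by a senior clinical psychologist. These features point towards the low end of the range. Against that, section 2.6 allows more time where clinically indicated, and none of these features shows that the ICC is zero.

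3. **The number of clinicians is unknown.** A reader might picture guidance delivered by a handful of people. The article says only that there are several, and recruitment runs for about three years. The 5-clinician rows are one end of a range, not a forecast.

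4. **The remedy is debatable.** In a single-centre trial, inference conditional on the participating clinicians is defensible. A log-link mixed model with a clinician effect would give a conditional contrast, different from the marginal means that section 3.2 reports. Few-cluster corrections cost power even if the ICC is 0: with 5 clinicians, about 3 to 5 points. This stands, and it is a reason not to insist on replacing the primary model. It does not weigh against a clinician-clustered version of the planned GEE alongside it.

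**Conclusion.** The point holds in conditional form. Guided participants are nested within clinicians, section 2.9 names no allowance for this, and section 3.1 describes only dependence over time. If outcomes correlate within clinician, both guided-arm contrasts will have intervals that are too narrow and less power than stated.

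The size rests on an ICC and a clinician count that the article does not give. It runs from negligible (ICC 0.01, 15 clinicians: roughly one point of power) to serious (ICC 0.05, 5 clinicians: about 17 points of power and nearly double the nominal error). To say outright that the interval is too narrow, or that the 80% is wrong, goes further than the document allows. It is nevertheless worth acting on, because the error favours a non-inferiority claim and the safeguard is cheap.

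**What to change.** **Section 3.1.** Prespecify that contrasts involving the guided arm are also estimated with the planned GEE clustered on the first-assigned clinician in the guided arm, each unguided and waitlist participant forming their own cluster, using a small-sample-corrected variance and degrees of freedom. At minimum this is a sensitivity analysis, and the non-inferiority conclusion must be reported alongside it. Report the clinician ICC. This keeps the marginal estimates on which section 3.2 relies.

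**Section 2.9.** State the expected number of clinicians. Restate the non-inferiority and guided-versus-control power as a range over that number and ICC 0.01 to 0.05, and say whether the non-inferiority test is one-sided 0.05 or 0.025.

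**Cost.** Wording in two sections and use of each guided participant's clinician identifier, which the clinic should already hold in order to run guidance and supervision. No extra patients, visits or staff. The price is wider guided-arm intervals, noticeably so if there are very few clinicians, and a less favourable stated power.

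### Section 3.1 judges maintenance at 3 and 12 months by within-group time effects, which test for no change and cannot by themselves show that the post-treatment gain was kept

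*Protocol article*

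**What the plan says.** Section 3.1 (Clinical efficacy) of the protocol article fixes the primary time point: "Post‐treatment is the primary endpoint for changes in the primary and secondary clinical outcomes". It then turns to durability. The purpose is to determine whether post-treatment "improvements are maintained over time, within‐group time effects will be examined", at 3 and 12 months. The next sentence reads "For all analyses, the level of statistical significance will be set at alpha 0.05", so that level covers these follow-up effects too. The model is also fixed: "All GEE models will include log‐link function and gamma scale parameters".

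The section does not say whether the time effect is measured from baseline or from post-treatment, which result would count as maintained, or how much loss could be tolerated.

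Two other places bear on the point:

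- Section 2.9 gives a "standard rate of symptom change on our primary outcomes of depression and anxiety of 24% each" and sets a non-inferiority margin: "we considered a difference of 50% of the standard rate of symptom reduction in depression and anxiety symptoms", that is 12 points. The margin is for unguided against guided at post-treatment, not for loss over time within an arm.
- Section 3.2 reports each group's average percentage improvement from baseline at post-treatment and at both follow-ups, taken from the GEE marginal means, and within-group effect sizes. No maintenance criterion is attached.

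**The concern.** Maintenance asks how much of the post-treatment gain has since been lost. A within-group time effect has a null of zero change, and that mismatch remains whichever contrast is meant.

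- **Follow-up against baseline.** A significant result shows only that some gain remains.
- **Follow-up against post-treatment.** Maintenance would have to be read from a non-significant result, which becomes more likely as precision falls.

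Long-term outcome is among the aims in the abstract. Under section 2.2 the waiting-list arm crosses over at about 6 months, so at 12 months no untreated comparator remains and the within-group statement carries much of any durability claim. The introduction reports dropout above 25% in two unguided epilepsy trials and 4% in a guided open trial. If the arms here differ in that way, the second contrast would favour the arm that loses more data.

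**Working it through.** **Inputs.** Gain 24 points (section 2.9). Sizes 125:80 for an 11-point difference and 125:125 for a 12-point margin (section 2.9). Evaluable participants per active arm: 150 × 0.80 = 120 (section 2.9 attrition). Alpha 0.05, taken as two-sided for the follow-up tests. Power 80%; the article prints this as "Type II error at β = 80" per cent, which I read as power.

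**The plan's own figures.** No figure is given for maintenance. The sample sizes cannot be rebuilt because no SD is stated and the inputs to the longitudinal software are not shown. I therefore solved simple two-group formulas for the SD:

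- 125:80, two-sided 0.05: 11 / [(1.960 + 0.842) × √(1/125 + 1/80)] = 27.4 points
- 125:125, two-sided 0.05: 12 / [(1.960 + 0.842) × √(2/125)] = 33.9 points
- 125:125, one-sided 0.05: 12 / [(1.645 + 0.842) × √(2/125)] = 38.2 points

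These differ, and I do not call that an error. They serve only as an assumed range for the SD of a within-arm change. With SE = SD/√120, the SEs are 2.50, 3.09 and 3.48 points.

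**Follow-up against baseline.** Probability of a significant remaining improvement = Φ((24 − loss)/SE − 1.96).

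| True loss | SD 27.4 | SD 33.9 | SD 38.2 |
|---|---|---|---|
| Half (12 points) | 0.998 | 0.973 | 0.931 |
| Three quarters (18 points) | 0.669 | 0.492 | 0.406 |

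**Follow-up against post-treatment.** Probability of missing the loss = 1 − Φ(loss/SE − 1.96).

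| True loss | SD 27.4 | SD 33.9 | SD 38.2 |
|---|---|---|---|
| Quarter (6 points) | 0.331 | 0.508 | 0.594 |
| Third (8 points) | 0.108 | 0.265 | 0.368 |
| Half (12 points) | 0.002 | 0.027 | 0.069 |

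If only 90 per arm contribute (an illustration), a loss of a quarter is missed in 45% to 68% of trials and a loss of a third in 21% to 49%.

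**Check on the log scale,** closer to the planned log-link model. The mean goes from 100 to 76 at post-treatment, n = 120, with a wider assumed range for the SD of log change. Half lost means a follow-up mean of 88; a quarter lost means 82.

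| Log SD | Half lost, still significant v baseline | Half lost, missed v post-treatment | Quarter lost, missed v post-treatment |
|---|---|---|---|
| 0.28 | >0.99 | <0.01 | 0.16 |
| 0.41 | 0.93 | 0.03 | 0.47 |
| 0.50 | 0.80 | 0.11 | 0.62 |
| 0.80 | 0.42 | 0.48 | 0.82 |

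**What an interval would show.** The 95% half-width for the change since post-treatment is 1.96 × SE = 4.9, 6.1 or 6.8 points. So even an observed change of zero is compatible with losing about 20% to 28% of a 24-point gain (4.9/24 to 6.8/24).

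**Would the 12-point margin do as a bound?** Suppose maintenance is claimed when the upper 95% limit for loss is below 12 points. When half the gain is truly lost, the false-claim rate is 2.5%. When 6 points are truly lost, Φ((12 − 6)/SE − 1.96) gives a claim in 67%, 49% or 41% of trials, against 33%, 51% or 59% that would pass through non-significance. At the smallest SD the borrowed bound is the more permissive rule.

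**The case against.** The best defence is that section 3.1 says only that the effects will be examined. It states no pass rule, and a condensed article may leave the contrast and the wording of conclusions to an analysis plan that is not shown. The sentence speaks of post-treatment improvements, so follow-up against post-treatment is the more natural contrast, and there a loss of half the gain would usually be found. Section 3.2 would print a fall from 24% to 12% beside the post-treatment figure. None of the three hypotheses in the introduction concerns maintenance.

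Most of this stands, and it limits the point. A reader might infer that the plan will declare lasting benefit after a substantial relapse. The documents do not support that: no such rule is written, the high pass rates belong to the baseline contrast only, the SDs are assumptions, and the relapse would be visible in the reported percentages. A reader might also infer that the 12-point margin is the plan's tolerance for relapse. It is not; section 2.9 sets it for a between-arm comparison at post-treatment.

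What does not stand is that this is only missing detail. Section 3.1 states a purpose and the tool for it. Naming the contrast later would not make a test of zero change bound the loss. For guided against unguided, section 2.9 does set a margin; nothing comparable is set for durability.

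**Conclusion.** The point holds as a mismatch between the stated question and the stated method, of moderate weight. Its size depends on which contrast is meant. The baseline contrast says little about how much gain was kept. The post-treatment contrast is much less exposed: at 120 per arm and SDs of 27 to 38 points it fails mainly for losses of about a quarter to a third of the gain, and it gets worse as follow-up data are lost. All these probabilities rest on an SD that the article does not give, one SD reused for every within-arm change, a normal approximation, and 120 evaluable per arm at follow-up. A larger SD weakens the baseline-contrast figure and worsens the post-treatment one. The primary post-treatment comparison is not touched.

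**What to change.** In section 3.1, replace the sentence on maintenance with:

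> For each active arm, the change from post-treatment to 3- and 12-month follow-up will be estimated from the GEE with a 95% CI, shown also as the share of the post-treatment improvement retained. Maintenance will be judged from this interval; neither a non-significant change from post-treatment nor a significant change from baseline will on its own be taken as evidence of maintenance.

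If the sponsor wants a yes/no claim, it should fix and justify a tolerable loss before the follow-up data are seen. The 12-point margin in section 2.9 should not be carried over without its own justification.

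The cost is a short replacement text and one further contrast from the same model, with no new data or participants. The downside is that some maintenance results will have to be reported as inconclusive.

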### Clinical significance

3.2

Clinical significance will be reported in several ways. Consistent with previous research,^32^ we will calculate the average percentage improvement (e.g. pre‐treatment mean score – post‐treatment mean score/pre‐treatment mean score) for each group from pre‐treatment to post‐treatment and 3‐ and 12‐month follow‐ups, for the clinical outcomes, using the estimated marginal means from the GEE models. Second, the proportion of participants achieving a clinical improvement (defined as ≥25%) and large clinical improvement (defined as ≥50%) on the primary outcomes will be calculated and compared between groups using generalized linear models using appropriate statistical models (e.g., GEE). In addition, deterioration (i.e., symptom increase at post‐treatment of ≥30% and within the clinical range) will be compared between groups. Based on these outcomes, the number needed to treat (NNT) will be calculated. Finally, Hedges *g* effect sizes will be calculated for the between‐group and within‐group effects.

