### Participant eligibility

2.3

Eligible participants will have a confirmed diagnosis of epilepsy, self‐report experiencing difficulties with their emotional health, be aged 18 years or over, and currently living in Australia.

Exclusion criteria include those who are imminently suicidal or unable to keep themselves safe, those experiencing severe cognitive difficulties with day‐to‐day memory, attention, and ability to learn basic information, those who are unable to read and understand English, or those who do not have access to the internet.

Non‐eligible applicants will be notified and strongly encouraged to speak to their primary health professional to identify local treatment options available to them. They may also be directed to the MindSpot Clinic (www.mindspot.org.au), which offers a variety of similar courses for free to all adults within Australia. A suicide risk assessment will be conducted for all participants and appropriate triaging to external community and crisis services where appropriate.

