Interested applicants will access a description of the study and the Participant Information and Consent Form on the eCentreClinic website. They will then elect to submit an online screening assessment, where they will complete an automated screening questionnaire to measure their symptoms and clarify that they meet the inclusion criteria.Potentially eligible participants will then be contacted by an eCentreClinic mental health clinician by telephone to complete a brief screening assessment and a structured clinical interview for DSM‐5 Mood and Anxiety Disorders (QuickSCID‐5; i.e., approx. 25 min). The purpose of this assessment is to ensure participants meet the inclusion criteria, have a complete understanding of the research, and have an opportunity to ask any questions they may have. It will also allow us to gather mental health diagnostic information for each participant, but this is not an inclusion criterion.Eligible participants will be sent an email confirming their position on the course. The email will contain a start date and information about the procedure for the first week of the course. On the first day of the course, participants are sent their login details with detailed instructions for working through the course. Participants are also provided with the contact details of the eCentreClinic Team and are invited to contact the Team via email in the event of technical issues. Participants in the guided group will be given instructions on how to contact their clinician. Thus, it is not possible to blind participants to group allocation.

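### The ≥25% and ≥50% improvement cut-offs have no baseline floor, so 1-point falls at very low scores count as response and dilute the responder comparison and the NNT

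*Protocol article*

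**What the plan says.** Section 3.2 (Clinical significance) of the protocol article plans to calculate "the proportion of participants achieving a clinical improvement (defined as ≥25%) and large clinical improvement (defined as ≥50%) on the primary outcomes" and to compare it between groups. No condition is placed on the baseline score or on the final score. The next definition, deterioration, is a rise in symptoms at post-treatment "of ≥30% and within the clinical range"; the article gives no value for that range. It then states: "Based on these outcomes, the number needed to treat (NNT) will be calculated".

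The eligibility rules let in low scores. Section 2.3 (Participant eligibility) asks only that people report "experiencing difficulties with their emotional health". Section 2.4 (Recruitment) says that the interview will collect diagnostic information, "but this is not an inclusion criterion". Section 2.7.3 makes the PHQ-9 and the GAD-7 primary for every participant. Section 3.1 analyses everyone randomised who has baseline data, whatever the score.

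**The concern.** A percentage rule with no floor means different things along the scale. A participant who enters mainly because of anxiety may score close to zero on the PHQ-9, and a mainly depressed participant close to zero on the GAD-7. On the scale where there is little to improve, one point can carry the label of clinical or even large clinical improvement. At baseline 0 the rule cannot be applied.

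These participants still enter the responder rates and the NNT. If they respond at much the same rate in every arm, they shrink the responder difference between arms and raise the NNT. The NNT would then describe a mixture of people with and without symptoms on that scale, in proportions the definition does not control.

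**Working it through.** The article gives no responder rate or NNT to reproduce, so the check runs from the definition.

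**Inputs.** Cut-offs of 25% and 50% (section 3.2); no entry score (sections 2.3 and 2.4); all randomised participants with baseline data (section 3.1). Assumption: both scales are scored in whole points from 0.

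**Step 1: smallest qualifying fall.** For baseline b and cut-off c, k = ceil(c × b).

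| Baseline | Fall needed for ≥25% | Fall needed for ≥50% |
|---|---|---|
| 0 | undefined | undefined |
| 1–2 | 1 | 1 |
| 3–4 | 1 | 2 |
| 5–6 | 2 | 3 |
| 9–10 | 3 | 5 |
| 20 | 5 | 10 |

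One point is large clinical improvement at baseline 1–2, and clinical improvement at 3–4. At baseline 20 the same labels need 10 and 5 points. This step depends only on whole-point scoring.

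**Step 2: how many people, and how often by chance.** The article does not give the baseline distribution. Assume an observed mean of 8–12, SD 5, scores that cannot fall below 0, a pre-post change SD of 2–4 and no true change. Simulation then gives:

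- 7–24% of participants at baseline 0–4;
- chance response at baseline 1–4 of roughly 18–34% for ≥25% and 13–25% for ≥50%.

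A more skewed (gamma) score distribution with the same mean and SD gives 10–28% and 7–19%, so these figures are only a guide.

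Compared with baseline 10 or more, the excess of chance response at low baselines is clear for ≥50% (about 17–24% against 2–4% at change SD 3). For ≥25% it is present at change SD 3 (about 23–31% against 15–22%) but reverses at change SD 4.

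**Step 3: dilution of the NNT.** Let a share s have low baselines and respond equally in both arms, and let the rest respond at an assumed 60% against 25%. The common low-baseline rate cancels, so NNT = 1 / [(1 − s) × 0.35].

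- s = 0: 1/0.35 = 2.9
- s = 7%: 1/0.3255 = 3.1
- s = 10%: 1/0.315 = 3.2
- s = 20%: 1/0.28 = 3.6
- s = 24%: 1/0.266 = 3.8
- s = 30%: 1/0.245 = 4.1

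If treatment also acts at low baselines (say 50% against 40%), the NNT at s = 10%, 20% and 30% is 3.1, 3.3 and 3.6, so the dilution is smaller.

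**Step 4: the same question with a treatment effect simulated.** With an assumed 35% reduction in true score, one example gives a ≥25% responder difference of 0.46 in all participants, 0.51 at baseline ≥5 and 0.60 at baseline ≥10. Mean 10 with change SD 3 gives values within 0.01 of these. The NNTs are 1/0.46 = 2.2, 1/0.51 = 2.0 and 1/0.60 = 1.7. The ≥25% difference was diluted in every setting tried. For ≥50% the dilution is smaller and can disappear when measurement error is low. The floors of 5 and 10 are illustrative only.

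**The case against.** The other side has several good points.

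- **The noise is easily overstated.** A simple normal calculation with change SD 3, 1 − Φ(0.5/3), suggests that 43% of participants at baseline 1–4 would meet ≥25% by chance. That ignores the floor at 0 and regression to the mean, and the simulated rates are lower. The ≥25% excess over high baselines is not robust. Dilution does not need that excess: it needs only a subgroup whose response differs little between arms.
- **A reader might infer that the plan tilts benefit against harm**, because only deterioration carries a clinical-range condition. A fall from 2 to 1 does count as large improvement, while a rise from 1 to 2 would not count as deterioration if it lies outside the range. But the condition most naturally applies to the post-treatment score, so it is not a baseline floor that improvement lacks. It also has an arithmetic reason: percentage increases from a small base are unbounded, whereas decreases stop at 100%. The article plans no benefit-to-harm comparison.
- **A reader might infer that this helps the non-inferiority hypothesis** by making guided and unguided care look alike. Section 2.9 sets the margin on symptom reduction and section 3.1 analyses scores by GEE. Responder rates decide neither superiority nor non-inferiority.
- **Baseline severity is partly covered.** Section 3.3 plans sensitivity analyses of the primary outcomes by baseline severity and DSM-5 status. These do not alter the responder definition or the NNT. A full analysis plan might supply the clinical-range value, which is no fault of an article, but the improvement definition is stated here without a floor.
- **Restriction has its own noise.** With mean 10 and an illustrative floor of 10, the chance ≥25% rate goes from 20% to 18% at change SD 3 but from 27% to 31% at change SD 4. The ≥50% rate falls in both cases (6% to 3%, 11% to 9%). This stands as a limit on how restricted rates may be read, but it acts equally in randomised arms.

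**Conclusion.** The point holds as a weakness in a secondary definition. It is certain that the rule labels 1-point falls at baseline 1–4 as improvement, that it is undefined at 0, and that the entry criteria admit such scores. The main consequence is diluted between-arm responder differences and an NNT that depends on the case mix.

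The size is not known, because the share of low baselines is not reported. Under the assumptions above (mean 8–12, SD 5; 60% against 25% response in symptomatic participants; no treatment difference at low baselines), an NNT of 2.9 becomes 3.1–3.8. It would be less if treatment also works at low baselines. The effect may therefore be modest. The documents do not support a claim that the primary conclusions are at risk, or that benefit is systematically favoured over harm. This is a cheap improvement to how clinical significance is reported.

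**What to change.** In section 3.2, for each scale separately:

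1. Report the ≥25% and ≥50% responder rates and the improvement NNT among randomised participants whose baseline on that scale is at or above a prespecified clinical cut-off. State its value, and use the same value for the range in the deterioration rule.
2. Keep the all-participant version alongside, with baseline 0 counted as non-responder.
3. State the denominator of each NNT, because deterioration stays in all participants.

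The restriction uses a score taken before treatment, so the comparison remains randomised. The cost is a few sentences and no new data. The downside is fewer participants per scale and wider intervals. Selecting on a high observed baseline also adds regression to the mean equally in all arms, so only the between-arm contrasts should be interpreted, not the restricted rates within an arm.
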